# Effectiveness and cost effectiveness of a stress management training for leaders of small and medium sized enterprises – study protocol for a randomized controlled-trial

**DOI:** 10.1186/s12889-021-10398-4

**Published:** 2021-03-08

**Keywords:** Stress, Stress management, Mental health, Stress management training, Leaders, Well-being

## Abstract

**Background:**

Leaders in small and medium-sized enterprises (SMEs) are exposed to increased stress as a result of a range of challenges. Moreover, they rarely have the opportunity to participate in stress management trainings. Therefore, KMU-GO (ger: Kleine und mittlere Unternehmen – Gesundheitsoffensive; en: small and medium-sized enterprises – health campaign) aims at conducting and evaluating such a stress management training. The focus of evaluation does not only lie on the effects on leaders participating but also on their employees.

**Methods:**

The study is planned as a 2 × 3 mixed design with two groups (intervention and waiting control group) as a between factor and point in time (at baseline, 6 and 12 months later) as a within factor. We aim at collecting data from *N* = 200 leaders. Based on the results of a preceding assessment, an already successfully implemented stress management training was adapted to SME needs and now serves as the framework of this intervention. The stress management training comprises one and a half days and is followed by two booster sessions (each 180 min) about 3 and 6 months after the training. The main focus of this intervention lies on specifying leaders stress reactivity while at the same time investigating its effects on employees’ mental health. Further dependent variables are leaders´ depression and anxiety scores, effort-reward imbalance, sick days and psychophysiological measures of heart rate variability, hair cortisol, and salivary alpha-amylase. Cost-effectiveness analyses will be conducted from a societal and employers’ point of view.

**Discussion:**

Stress management is a highly relevant issue for leaders in SMEs. By providing an adequate occupational stress management training, we expect to improve leaders´ and also employees` mental health, thereby preventing economic losses for SMEs and the national economy. However, collecting data from employees about the success of a stress management training of their leader is a highly sensitive topic. It requires a carefully planned proceeding ensuring for example a high degree of transparency, anonymity, and providing team incentives.

**Trial registration:**

The KMU-GO trial is registered at the German Clinical Trial Register (DRKS): DRKS00023457 (05.11.2020)

## Background

Holding a leadership position comes along with increased responsibility and high job demands. Leaders need to make decisions for the benefit of their company and, at the same time, to ensure that performance and satisfaction of their employees remain high. Employees in leadership positions are thus easily exposed to high levels of occupational stress [1] putting them at risk for the adverse health effects of prolonged stress exposure (cf. [2]). On the organizational level, high levels of work stress may impair job performance [3, 4] as well as job satisfaction [5] and may increase absenteeism and turnover intention [6, 7]. Due to its negative effects on staff turnover and productivity occupational stress is estimated to cause economic losses for companies and the national economy amounting to EUR 617 billion € per year in the EU [8]. For the individual leader, the risk to develop stress-associated diseases such as cardiovascular diseases [9], coronary heart diseases [10], pain [11], depression [12] and burn-out [13, 14] is elevated. Potential mechanisms include stress induced dysregulation of autonomic [15, 16], hormonal [17] and metabolic systems (Jarczok et al. 2013, [18]). But also personality and health behaviour play a role [19].

Besides being stress-impaired themselves, high work stress among leaders may also impact the mental health, job satisfaction and well-being of their employees in short and long-term. For example, Schmidt et al. [20] could show in a 10-year follow-up that a lack of supportive leadership behaviour predicted suboptimal self-rated health independent of job strain n a large general population sample. Similarly, Franke et al. [21] suggest that leaders influence their employees’ health in multiple ways, by having a role model function, through their own stress, their leadership style, and by shaping working conditions. First, highly stressed leaders are more likely to exert pressure onto their staff and elicit distress and strain in their employees, a phenomenon known as ‘emotional contagion’ [22–24]. Second, high stress levels may impede leaders from exerting a stress-preventive leadership style [25]. Instead, they might adopt a rather negative or destructive leading style [26]. Third, implementing stress-preventive working conditions may be less of a priority when leaders experience high stress themselves.

This is especially relevant in small and medium-sized enterprises (SMEs) since leaders may be exposed to particularly high stress and work load: Managerial decisions in SMEs are often made by one person only or a small number of people on the management board [27]. The effects of such decisions are often more immediate and high stakes than in large enterprises, which may offset financial losses caused by unfavourable decisions against other revenue sources [28]. In SMEs, personnel is limited and thus positions often come with multiple roles and broad task responsibilities as opposed to a narrower and more specialized division of work in large companies [29]. Leaders in SMEs have no or only few co-workers on the same hierarchy level and therefore have less opportunity to consult and exchange views with their peers for support (Thorpe et al., 2009). In addition, the personal identification with the job is higher in SMEs, especially in family-led corporations or own enterprises, and boundaries between personal and professional lives tend to blur [30]. This might exacerbate the risk that work stress continues to dwell during after-work hours and may impede recovery and relaxation during the free time [31].

Skillful leadership and stress management competencies can help prevent excessive occupational stress which not only is important for the companies proximal goals (employees satisfaction and absenteeism), but also mitigates the risk for stress-related health issues [23]. Improved stress coping skills in leaders have multiplier effects as they improve leaders’ stress reactions and reduces their employees exposure to work stress [32]. This creates the need for effective, empirically evaluated stress management trainings [33].

Ideally, stress-prevention measures target both, individual and organization-related approaches [34, 35]. Integrated approaches tackle work-related stress on a behavioural level equipping employees to best react and cope with stressors. Simultaneously, they aim to improve organizational structures, and foster health-promoting working conditions and company cultures. In the short-term, however, organizational level prevention measures are more difficult to practically implement than individual-level approaches [36]. In the empirical literature, most stress management interventions thus address behaviour change that can be employed on the individual level. Interventions that use methods derived from cognitive behavioural therapy show the best empirical support or effectiveness on reduction of perceived stress and depressive symptoms [34, 37].

When implementing such stress intervention programs, large companies seem to be better equipped than SMEs when it comes to the required resources and structures [38]. However, in SMEs, the supply of such interventions and tools is much more limited [28]. With the majority of all German companies belonging to the SME-sector (99.3%) and most of the workforce working in SMEs (61.2% [39]), it is important to close this gap and to provide low-threshold trainings that target effective leadership and stress-management [40]. However, research on stress prevention and well-being interventions that target SMEs specifically are scarce [41]. In their meta-analysis, Gerhardt and colleagues call for more research on stress prevention in SMEs and conclude from existing trials that individual-related approaches showed the most promising results to reduce stress at work (2019). In sum, leaders in SMEs are at a particular risk of excessive work stress and its adverse consequences but have been neglected in stress intervention research [42, 43]. We expect that this target group might particularly benefit from stress management trainings and that the demand for such prevention programs might be high.

Beyond its direct impact on the health of leaders and co-workers, worksite mental health interventions are also expected to prevent economic losses to the individual company and the national economy at a whole. At the company level economic effects can be achieved through the reduction of absenteeism and staff turnover, while at the societal level the prevention of chronic disability, long-term unemployment and early retirement are particularly important [8, 44–47].

One intervention that showed prolonged beneficial effects on leaders’ perceived stress is the MAN-GO stress-management training that was conducted in a large steel manufacturing company comprising only male leaders [48]. The intervention reduced perceived stress among leaders and continued to show beneficial effects even after a nine-year follow-up evaluation [49]. The purpose of the present study is also to replicate the findings of the previous longitudinal MAN-GO intervention study and to prove whether its effectiveness generalizes to the SME sector, all genders and all industries. To this end, we adapted the original manual from the MAN-GO training in order to target leaders of both sexes in SMEs. The one and a half days stress management training includes elements from cognitive behavioural therapy, psychodynamic psychotherapy, psychoeducation and mindfulness components and is followed by two booster session (each 180 min) three and 6 months afterwards.

### Aims and objectives

In analogy to the original research design, we will assess self-reported perceived stress and reactivity to stress and symptoms of anxiety and depression as the main outcome variables. To complement the subjective measures, physiological markers of stress (resting blood pressure, indicators of heart rate variability, hair cortisol levels and salivary alpha-amylase) will be measured in the leaders. Assuming that leadership behaviour and leaders’ individual stress levels impact the work stress of their employees, we will assess the effects of the intervention on the leaders’ employees as well. Therefore, employees will rate their own perceived work stress and the leadership behaviour of their superior on questionnaires before and after the stress intervention. Furthermore, the intervention will be evaluated in the light of its economic and organizational benefits: secondary evaluation criteria will therefore be number of sick days, physiological health, and absenteeism, the relationship between leaders and employees as assessed by leaders and employees, and their perception of working conditions.

The study is designed as a randomized controlled trial with a waiting control group evaluating the effectiveness of a stress management training at 6 and 12-months-follow-up measurement time points.

In short, the main objectives of KMU-GO are:
To investigate the effectiveness of a stress management training for leaders based on their subjectively perceived mental health and objective physiological markers of stress as well as other outcome variables such as anxiety and depressive or psychosomatic symptoms or sick days in comparison with a waiting control group.To investigate indirect effects on the subjectively perceived mental health of the employees of the trained leaders as well as on their emotional and cognitive irritation, well-being, perception of working conditions and the quality of leader-employee relationship.To evaluate the cost-utility of the stress management training from a societal perspective.To replicate the effects of the previous MAN-GO [48] study, thereby expanding the results to all genders, the SME sector and all industries.To additionally evaluate the cost-effectiveness of the stress management training at the company and societal level

### Trial design

The study is designed as a randomized 2 × 3-mixed design (factor 1 (group): intervention or waiting control group; factor 2 (point in time): baseline, 6 months and 12 months later; see Fig. 1). All participating leaders are going to be randomly assigned to one group. Baseline measures of participants of the intervention group are going to be collected about 2 weeks before their group intervention takes place. Baseline measures of participants of the waiting control group are going to be collected simultaneously. The intervention group is going to take part in the stress management training, followed by two booster sessions after 3 and 6 months. Participant’s satisfaction with the intervention is planned to be assessed within 2 weeks after the intervention. After 6 and 12 months, all relevant outcome variables are planned to be measured (for more detailed information about the outcome variables, please see Section 2.3). The waiting control group will also be measured for all relevant outcome variables after 6 and 12 months, but is going to take part in the intervention only after the last measurement. Employees of the participating leaders will be measured at the same points in time: baseline, 6 and 12 months later.

**Fig. 1 Fig1:**
[figure not shown]
Trial Design

## Method

### Population and sample size

#### Leaders

The target group are leaders of small and medium-sized enterprises (SMEs). We define SMEs as enterprises with up to 500 employees [50, 51] without regarding the annual sales. Leaders of all genders aged between 18 and 65 years are allowed to participate as long as they are not about to retire within the next year. A sample size of *n* = 100 participants in the intervention group and *n* = 100 participants in the waiting control group is planned (*N* = 200 participants).

The sample size calculation was performed using G*Power3.1. Based on a 2 × 3-mixed design (factor 1 (group): intervention or waiting control group; factor 2 (point in time): baseline, 6 months and 12 months later) the required sample size for a MANOVA with measurement repetition was estimated using the following predefined parameters: mean effect size f = .25 (Ω = 0.06), α-error = .05, test strength 1-β = .80. This results in a required sample size of *n* = 158 participants (*n* = 59 per group). The calculation of the required sample size was based on the procedure proposed by Prajapati et al. (2010) to calculate the required sample sizes for all possible effects (within, between, interaction) of the present design and to use the largest calculated sample size. Due to the high effort of the outcome criteria to be collected (e.g., saliva samples, 24-h heart rate variability) a high lost-to-follow-up as well as numerous missing values can be expected. We therefore calculate with a total failure rate of 21% (lost-to-follow-up and due to missing values), resulting in a required sample size of *N* = 200 (*n* = 100 per group at T_0_).

Recruitment is carried out in cooperation with AOK Baden-Württemberg, IHK Ulm, IHK Reutlingen, Offensive Mittelstand, Handwerkskammer Ulm, and Südwestmetall. Flyers and advertising texts will be sent via email through suitable channels and presented at suitable events (face-to-face and online). Leaders who want to participate in this study have to be aged between 18 and 64 years, need to sign the informed consent (see appendix), and must have sufficient German language skills. Due to the variety and size of the above mentioned cooperation partners, the achievement of the targeted sample size can be considered as realistic. Moreover, leaders will be reminded by email to take part in the follow-up measures. As the participation is voluntary, consent may be withdrawn without any reason. The protocol was approved by the institutional ethics committee.

#### Employees

In addition to the leaders participating in the intervention, we also aim to at surveying their employees in order to gather data on the indirect effects of the intervention. Thus, leaders will be informed in advance about the additionally planned and voluntary survey of their employees. Upon prior written consent, leaders will receive information material in order to inform their employees adequately about the study and their ways to participate: (1) qualitative serial interview at T0 and T2 (only intervention group) and/or (2) online survey at T0, T1 and T2. Due to the so far unknown team size, a sample size calculation pertaining to the online survey cannot be performed. On average, we expect three employees per leader to fill in the questionnaires, resulting in a total of *N* = 300 employees per group. Regarding the qualitative serial interviews, we aim to interview *N* = 25 employees (intervention group only) at T0. Thus, we consider a conservative drop-out rate of 40% with the aim of being able to interview *N* = 15 employees at T2.

The randomization of employees is based on the group allocation of their leaders (convenience sampling). Employees of leaders who want to participate in this study have to be aged between 18 and 65 years, need to sign the informed consent, and must have sufficient German language skills in order to complete the online questionnaire or to be interviewed, respectively.

Although leaders can decide on their own whether to involve their employees or not, we will encourage leaders to do so by highlighting the importance of employees’ inclusion. Moreover, we offer anonymous employee summary reports after T2 to each leader, if the following conditions are met: (1) Their employees agree to the anonymous disclosure of results in a summary form (last question in online survey) and (2) ≥ 5 employees per leader provide data.

First, employees will be informed by their leader, preferably in 1-on-1 or small group meetings. Here, employees will also receive written information about the conditions of participation. Second, direct contact is established between employees and study team in order to ask further questions or gain additional information, if necessary. Following verbal and written information, employees can decide voluntarily whether to participate. All participants at T0 are going to be reminded by email to participate again at the follow-up measures. As the participation is voluntary, consent may be withdrawn without reasons that need to be disclosed.

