#### Statistical methods

Data will be analysed using the statistic software IBM SPSS Statistics 27. Descriptive analyses will be conducted after the baseline. A multivariate analysis of variance (MANOVA) with all relevant outcome parameters as specified above will be calculated in order to test the effects of the intervention on different dependent variables. Potential covariates will be included in the analysis. Therefore, if relevant covariates occur, a MANCOVA will be performed instead of the MANOVA. A covariate will be identified as such, if a demographic variable will correlate with the outcome variable or if there is a significant difference between the intervention group and the waitlist control group across this variable.

To evaluate the effects of the stress management intervention more specifically, changes in outcome variables will be analysed by two-factorial ANOVA with repeated measures and group (intervention vs. waiting control group) as a between-person effect. The core hypothesis is that perceived stress and physiological stress parameters of leaders will significantly decrease from baseline to follow-up measurements for participants in the intervention group. Thus, we will test the interaction effect of time x group for the different outcome variables. Where necessary, Bonferroni correction will be applied to avoid inflation of the type one error by multiple comparisons.

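### Employees are allocated through their leader, but the only stated effect analysis has no leader term; applied to objective 2, it understates standard errors when change is correlated within teams

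*Protocol article*

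**What the plan says.** The Employees subsection (Protocol article, Population and sample size) allocates staff through their superior: "The randomization of employees is based on the group allocation of their leaders (convenience sampling". Under Assignment of interventions, the unit actually randomised is the single leader. For leaders, "A sample size of *n* = 100 participants in the intervention group and *n* = 100 participants in the waiting control group is planned".

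The employee number is an expectation: "On average, we expect three employees per leader to fill in the questionnaires, resulting in a total of *N* = 300 employees per group". It follows the statement "Due to the so far unknown team size, a sample size calculation pertaining to the online survey cannot be performed", so no power, effect size or ICC is attached to it.

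Objective 2 under Aims and objectives is the indirect effect on employees' mental health, irritation, well-being, working conditions and relationship with the leader. The Trial design section measures employees at the same three visits as leaders.

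Statistical methods plans a MANOVA on all relevant outcomes, and then "changes in outcome variables will be analysed by two-factorial ANOVA with repeated measures and group", with group as a factor between persons and the time by group interaction as the test of interest. No leader or team term, cluster-robust error or team-mean analysis appears, and nothing there is specific to employees.

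**The concern.** Employees of one leader share that leader and the workplace they are asked to rate. The Background section says that leaders affect their staff's health by acting as role models, through their own stress, through leadership style and by shaping working conditions. If any of these shifts during the 12 months, the whole team tends to shift with it. This happens in both arms and for reasons unrelated to the training. Changes reported by colleagues are then not independent pieces of evidence about the training.

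An ANOVA whose error term is variation between persons treats them as independent. Its intervals for the employee effect come out too narrow and its p-values too small. The abstract puts the effect on employees at the centre of the evaluation, and a false positive there would support a claim that training leaders benefits their staff.

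**Working it through.** **Inputs from the documents.** Leaders per arm: 100 (Leaders subsection). Mean respondents per leader: m = 3 (Employees subsection). Test: group by time over three visits, hence 2 df (Statistical methods).

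**Assumed, because the documents give no figure.** ICC of change within a leader's team: 0.05, 0.10, 0.20, 0.30.

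**The plan's own figure.** 100 leaders x 3 = 300 per group. It reproduces exactly and is a head count.

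**Formulas.**
- Design effect: DE = 1 + (m - 1) x ICC
- Effective number per group: 300 / DE
- Factor by which the unadjusted standard error is too small: sqrt(DE)
- Actual error of a nominal 5% test, 1 df: 2 x (1 - Phi(1.96 / sqrt(DE)))
- The same for 2 df: exp(-5.99 / (2 x DE))

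Example at ICC 0.20: DE = 1 + 2 x 0.20 = 1.40; 300 / 1.40 = 214; sqrt(1.40) = 1.18; 1 df: 2 x (1 - Phi(1.96 / 1.18)) = 9.8%; 2 df: exp(-5.99 / 2.80) = 11.8%.

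| ICC of change | DE | Effective n per group | SE factor | Error, 1 df | Error, 2 df | Simulated, 2 df |
|---|---|---|---|---|---|---|
| 0.05 | 1.10 | 273 | 1.05 | 6.2% | 6.6% | 6.8% |
| 0.10 | 1.20 | 250 | 1.10 | 7.4% | 8.2% | 8.4% |
| 0.20 | 1.40 | 214 | 1.18 | 9.8% | 11.8% | 11.8% |
| 0.30 | 1.60 | 188 | 1.26 | 12.1% | 15.4% | 14.8% |

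The last column simulates the unadjusted repeated-measures ANOVA under no training effect, with 100 teams of 3 per arm, a team effect drawn afresh at each visit, and 8,000 runs. At ICC 0 it gives 4.9%.

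**Which correlation matters.** When the simulated team effect is held constant over the three visits at ICC 0.20, the error is 4.6%. The simulation's own standard error is sqrt(0.05 x 0.95 / 8000) = 0.24 percentage points, so this is compatible with 5%. A stable team effect cancels in the interaction; only correlated change inflates the error.

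**Team size.** The same 300 made up of 60 leaders with 5 respondents each gives DE = 1 + 4 x ICC = 1.20 to 2.20, an effective number of 250 to 136, and a 1-df error of 7.4% to 18.6%. Unequal teams with mean 3 and an assumed coefficient of variation of 0.5 give DE = 1 + ((1 + 0.25) x 3 - 1) x ICC = 1.14 to 1.83, an effective number of 264 to 164, and a 1-df error of 6.6% to 14.7%.

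**The case against.** **The employee analysis is inferred.** Statistical methods words its core hypothesis for leaders and never says in terms that employee outcomes get a person-level ANOVA. The article is condensed, and an analysis plan may hold a separate employee model. This stands as a limit on the claim. It does not remove it: the section covers all relevant outcomes, the employees sit in the same three-visit design, and no other method is offered. The point concerns the method the article does fix.

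**The 300 claims no precision.** A reader might infer that the plan overstates the power of its employee survey. It does not: the preceding sentence disclaims any calculation, so no stated power figure is wrong. A reader might also take that disclaimer to be false. That goes too far. The obstacle named is unknown team size, and any calculation needs an ICC that the documents do not give. A range could have been shown, but that is advice.

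**Attrition cannot be read across from leaders.** It is tempting to cut the 300 by the leaders' 21% failure rate. That rate includes missing values and is justified by demanding measurements made only on leaders. A leader without usable saliva or heart-rate data does not remove a team, and employees get their own survey link and reminders. Nor does an average of three require every leader to involve staff, since an average can include leaders who contribute none.

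**The size is assumed.** Much of what a team shares may be stable and cancel. At an ICC of change of 0.05 with teams of three, the inflation is modest. This is correct, and the range has to be given with that caveat.

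**Conclusion.** The point holds in this form: for employees the leader's team is the randomised unit, and the stated analysis has no term for it. Used for objective 2, that analysis understates standard errors by a factor of about 1.05 to 1.26. A nominal 5% test then runs at about 6 to 12% (1 df) or 7 to 15% (the planned 2-df interaction), and 300 per group carries the information of about 273 to 188 independent employees.

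These figures rest on 100 leaders per arm with 3 respondents each and an assumed ICC of change of 0.05 to 0.30. Larger or unequal teams make them worse; if teams share only stable differences, the group by time test keeps its level. The Background section's account of how leaders affect staff gives reason to expect some correlated change, so independence should not be the working assumption. The documents do not show that the sample-size text states a wrong precision, or that any particular false positive rate will occur. The comparison of leaders is not touched by this point.

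**What to change.** Add to Statistical methods that employee outcomes are analysed with clustering by leader taken into account. One suitable form is a linear mixed model with arm by visit, a random intercept for employee, and random effects for leader and leader by visit. The leader-by-visit effect matters because it carries the correlated change. Cluster-robust standard errors by leader would serve equally well. So would team means per leader and visit, which keep the planned repeated-measures ANOVA with one record per leader.

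In the Employees subsection, describe 300 per group as the expected head count of respondents and give its effective size over a stated ICC range; the table above can be used for 0.05 to 0.30.

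Confirm that the link between employee and leader is kept for analysis. It is already needed to assign employees to arms and to produce the per-leader summary reports, so the identification code need not change.

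The cost is a few sentences of analysis wording and a less favourable effective number. Design, recruitment and data collection stay as they are. The wording should be settled before employee data are analysed.
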